### 13.2 Clinical laboratory abnormalities and other abnormal assessments as AEs and SAEs

Abnormal laboratory findings (e.g., clinical chemistry, haematology, urinalysis) or other abnormal assessments (e.g., ECGs, X-rays and scans) that are judged by the investigator as clinically significant will be recorded as AEs or SAEs if they meet the definitions given above. By definition, **all clinically significant Grade 3 or 4 laboratory abnormalities should be reported as SAEs.**

Clinically significant abnormal laboratory findings or other abnormal assessments that are detected during the study or are present at baseline and significantly worsen following the start of the study will be reported as AEs or SAEs. However, clinically significant abnormal laboratory findings or other abnormal assessments that are associated with the disease being studied, unless judged by the investigator as more severe than expected for the patient's condition, or that are present or detected at the start of the study and do not worsen, will not be reported as AEs or SAEs.

The investigator will exercise his or her medical and scientific judgment in deciding whether an abnormal laboratory finding or other abnormal assessment is clinically significant.

### 13.3 Determining adverse event causality

The Investigator will assess and classify the relationship of an AE to the trial IMP as follows:

| Classification   | Relationship     | Definition                                                                                                                                                                                                                                   |
|------------------|------------------|----------------------------------------------------------------------------------------------------------------------------------------------------------------------------------------------------------------------------------------------|
| drug-related     | Almost certainly | 
 
Starts within a time related to the study drug administration and
 
No obvious alternative medical explanation.
 
                                                              |
|                  | Probably         | 
 
Starts within a time related to the study drug administration and
 
Cannot be reasonably explained by known characteristics of the patient's clinical state.
 
                 |
|                  | Possibly         | 
 
Starts within a time related to the study drug administration and
 
A causal relationship between the study drug and the adverse event is at least a reasonable possibility.
 
 |
| not drug related | Unlikely         | 
 
The time association or the patient's clinical state is such that the study drug is not likely to have had an association with the observed effect.
 
                                        |
|                  | Unrelated        | 
 
The AE is definitely not associated with the study drug administered.
 
                                                                                                                      |

The Investigator must endeavour to obtain sufficient information to confirm the causality of the adverse event (i.e. relation to surgery, study drug, background treatment, other illness, progressive malignancy etc) and give their opinion of the causal relationship between each AE and study drug. This may require instituting supplementary investigations of significant AEs based on their clinical judgement of the likely causative factors and/or include seeking a further specialist opinion.

### 13.4 Expected adverse events

Section 5 of the IB for BKM120 lists all the expected side effects associated with the use of BKM120. A copy of this document must be held in the Site File for reference.

Thoracic radiotherapy treatment is often associated with side effects such as fatigue, oesophagitis, pneumonitis, and nausea. However with the palliative doses of radiotherapy that will be used in this trial, these side effects are usually mild and resolve within a few weeks of completing treatment. If a patient experiences more severe side effects, the Investigator will decide whether these have occurred as a result of BKM120 or its interactions with radiotherapy treatment, based on the severity of symptoms and other clinical information such as the radiotherapy volumes.

### 13.5 Suspected Unexpected Serious Adverse Drug Reactions (SUSARs)

A Suspected Unexpected Serious Adverse Drug Reaction (SUSAR) is a serious adverse reaction, the nature or severity of which is not consistent with the applicable product information (e.g. Investigator's Brochure for an unapproved investigational product or SPC for an approved product). SUSARs therefore are suspected to be at least possibly related to the study agent, fulfil the definition of a SAE, the nature and severity of which are not consistent with the applicable product information. In addition, other safety issues qualify for expedited reporting where they might materially alter the current risk assessment of an IMP or be sufficient to change IMP administration or the overall conduct of the trial. Responsibility for expedited safety reporting to responsible authorities will be done by the trials office using their own internal OCTO SOPs.

### 13.6 Expedited reporting of SAEs

The following SAE reporting requirements apply regardless of the Investigator's assessment of the causality or expectedness of the SAE. All SAEs should be reported on the trial SAE paper report form (see SAE report form and completion guidelines).

**SAE reports must be sent within 24 hours of site staff becoming aware of the event to either:**

**PV Email:** [contact]  
**OCTO [contact]

- If the SAE has not been reported within the specified timeframe, a reason for lateness must be provided when sending the SAE Report Form.

- Investigators should also adhere to their local Trust policy for incident and SAE reporting in research.

-OCTO will be responsible for reporting all SAEs to Novartis within 24 hours of receiving an SAE report.

### 13.7 Follow-up of Serious Adverse Events

If new or amended information on a reported SAE becomes available, the Investigator should report this on a new SAE Report Form using the completion guidelines. Extra annotated information and/or copies of test results may be provided separately. If using the original form to notify further information, all new or amended information must be initialled and dated so that all changes are clearly identified.

Follow up will continue until all the necessary safety data for the event has been gathered. Follow up information must be sent to the trials office within one working day of the site becoming aware. Any SAE that is ongoing when a subject completes his/her participation in the trial must be followed until any of the following occurs:

- The event resolves or stabilizes;
- The event returns to baseline condition or value (if a baseline value is available);
- The event is attributed to other agent(s) or to factors unrelated to study conduct.

SAEs that are considered to be definitely unrelated to the trial intervention will not be followed up and monitored. SAEs must be reported until 6 weeks after end of treatment.

### 13.8 Reporting Adverse Events on the CRF

All AEs, including Serious AEs (except those described in section 13.9) must be recorded on the case report forms (CRF) for that patient. Please note that AEs are recorded on eCRFs within OpenClinica and SAEs are additionally recorded on the paper SAE report form and emailed/faxed to OCTO. The information provided will include date of onset, event diagnosis (if known) or sign/symptom, severity, time course, duration and outcome and relationship of the AE to study drug. Any concomitant medications or other any therapy used to treat the event must be listed. The Investigator will provide an "other" cause for serious AEs considered to be unrelated to the study drug. Sites should ensure data entered into the CRF is consistent with the SAE report information where applicable.

Each separate AE episode must be recorded. For example, if an AE resolves completely or resolves to baseline and then recurs or worsens again, this must be recorded as a separate AE. For AEs to be considered intermittent, the events must be of similar nature and severity

The NCI CTCAE Version 4.0 must be used to grade each AE, and the worst grade recorded.

### 13.9 Events exempt from being reported as AE/ SAEs

This section specifies adverse events that do not require reporting providing the Investigator is certain that they are as expected given the natural course of the disease under study and /or expected outcomes of any background routine standard of care. The event must be reported if the Investigator cannot exclude the possibility that any trial intervention (including tests and other procedures) might be causally implicated or if the frequency, severity or pattern of events is not as expected for the patient's condition.

#### *Progression of underlying disease*

Disease progression and resultant death will be captured on the eCRF. Adverse events including hospitalisation and/or death that are clearly consistent with disease progression will not be reported as individual AE/SAEs. Clinical symptoms of progression will only be reported as adverse events if the symptom cannot be determined as exclusively due to the progression of the underlying malignancy, or does not fit the expected pattern of progression.

Every effort should be made to document the objective progression of underlying malignancy. In some cases, the determination of clinical progression may be based on symptomatic deterioration. For example, progression may be evident from clinical symptoms, but is not supported by tumour measurements. Or, the disease progression is so evident that the investigator may elect not to perform further disease assessments.

#### *Death on study*

The patients enrolled into this study will have incurable NSCLC which is associated with a poor prognosis. It is therefore likely that some patients will die as a result of their underlying malignancy whilst enrolled in this study. Death due to NSCLC will be recorded on the Death eCRF form providing no causal relationship with BKM120 is suspected. The investigator will state whether the death was expected or unexpected.

### 13.10 Informing Investigators of new safety information

The Chief Investigator will ensure that all investigators are kept informed in a timely manner, as new safety profile information becomes available. Investigators are responsible for briefing their study team and onward transmission to their local ethics committees and/or R&D office as appropriate.

## 14 PREGNANCY

Pregnancies (in a participant or partner) occurring whilst taking BKM120 treatment must be reported. A pregnancy notification form should be completed and emailed/faxed to the trial office within the same timelines as an SAE. All reported pregnancies should be followed and the outcome reported using the same form.

**Note:** Pregnancy is only considered an AE/SAE if there is reason to believe it may be the result of an interaction between the study IMP and the contraceptive used.

Women who become pregnant must be withdrawn from BKM120 treatment at the earliest opportunity.

All reported pregnancies should be followed up until term. If the outcome of the pregnancy meets any of the criteria for seriousness, it must also be reported as an SAE. Examples of pregnancy outcomes that are SAEs include reports of:

- congenital anomalies or developmental delay, in the foetus or the child.
- foetal death and spontaneous abortion
- suspected adverse reactions in the neonate that are classified as serious

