### Non-clinical safety pharmacology and toxicology

Safety pharmacology studies in rats revealed no effects on neuronal (behaviour) or respiratory functions. Cardiac safety studies, conducted in vitro and in vivo did not indicate a prominent electrophysiological risk. No relevant electrophysiological effect was seen in dogs. The only effect considered relevant was a trend toward an increase in systolic and diastolic blood pressure, which was observed in two dog telemetry studies. In rats and dogs, clinical pathology and histopathology findings showed quantitative reductions of lymphoid and erythroid counts and lymphoid tissue hypoplasia.

The pancreas was seen to be affected by treatment with BKM120, particularly in dogs, where acinar cell toxicity was seen in the exocrine part of this organ. At higher doses in the 2-week dose-range-finding study in rats, there were histopathological findings in both the endocrine as well as the exocrine pancreas.

Male sexual organs and associated tissues were found to be targets of toxicity in both rats and dogs. Changes included minimal to slight germ cell depletion, formation of spermatid giant cells and abnormal spermatids, and cellular debris in epididymal tubules. Testicular toxicity did not fully reverse after the 4-week treatment-free period in rats (highest dose), although a clear trend towards recovery was seen. In individual female rats, minimal to slight cyst formation occurred in the Graafian follicles. In dogs, there was no effect on female sexual organs.

Glucose homeostasis was affected in various species (mice, rats, dogs), as expected from the mode of action of BKM120. However, these effects were minimal in both rats and dogs at the doses used in the 4-week studies.

Other safety considerations include:

- After up to 2 weeks of treatment with up to .5mg/kg/day of BKM120, alterations in the levels of multiple brain neurotransmitters were seen in rats.
- No evidence for a direct DNA interaction was found in an Ames test and two chromosome aberration tests in vitro with BKM120. However, evidence of a genotoxic potential with BKM120 has been seen in vitro and in vivo and is likely due to an aneugenic effect.
- No phototoxic potential or any effect on wound healing has been identified with BKM120 in pre-clinical studies.

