  - Surgical sterilization: Have had bilateral oophorectomy (with or without hysterectomy) or tubal ligation at least six weeks before taking BKM120. In case of oophorectomy alone, only when the reproductive status of the woman has been confirmed by follow up hormone level assessment.
  - Male partner sterilization (with the appropriate post-vasectomy documentation of the absence of sperm in the ejaculate). [For female study patients, the vasectomised male partner should be the sole partner for that patient]
  - Or use of a combination of any two of the following (a+b):
    - a) Placement of an intrauterine device (IUD) or intrauterine system (IUS)
    - b) Barrier methods of contraception: condom or occlusive cap (diaphragm or cervical/vault caps) with spermicidal foam/gel/film/cream/vaginal suppository

Female patients must use acceptable methods of contraception must continue to use contraception for at least 4 weeks after completing BKM120. Male patients (and their female partners) will need to continue to use contraception for at least 16 weeks after completing BKM120.

**Women of child-bearing potential must have a negative serum pregnancy test  $\leq$  72 hours prior to initiating treatment**

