#### ***Contraceptive/ Pregnancy counselling***

All participants must be advised on the need to use reliable methods of contraception during the study. The advice should include:

- (1) The acceptable methods, including: male or female sterilization, some intrauterine devices (IUDs), and abstinence.
- (2) The recommendation that a barrier method should be used in addition to another form of contraception.
- (3) Males should continue to take these precautions for a minimum of 16 weeks after the last dose of study drug. Female partners of men enrolled in the study should continue to use acceptable methods of contraception for 16 weeks after the final dose of BKM120.
- (4) Female patients in the study should continue to take these precautions for a minimum of 4 weeks after the last dose of study drug.

- (5) That any pregnancy that occurs during administration of the study drug will be followed up and the outcome of all pregnancies (spontaneous miscarriage, elective termination, normal birth or congenital abnormality) will be reported and followed up even if the participant is discontinued from the study.

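### Required pregnancy notification stops with BKM120 dosing, while required contraception runs 4 weeks (female patients) or 16 weeks (male patients and partners) longer

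*Protocol*

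**What the plan says.** Two places in the protocol set the period for pregnancy reporting, and both stop with dosing. Section 14 states: "Pregnancies (in a participant or partner) occurring whilst taking BKM120 treatment must be reported". Item (5) of the counselling list in Section 5.1 tells participants that "any pregnancy that occurs during administration of the study drug will be followed up". The further duties in Section 14 (follow-up to term, SAE reporting of serious outcomes) apply to pregnancies that have been reported, so they depend on the same period.

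Two places set the period for contraception, and both go past dosing. Exclusion criterion 21 in Section 4.1 says that female patients "must continue to use contraception for at least 4 weeks after completing BKM120", and that "Male patients (and their female partners) will need to continue to use contraception for at least 16 weeks after completing BKM120". Items (3) and (4) of the Section 5.1 list agree: "Males should continue to take these precautions for a minimum of 16 weeks after the last dose of study drug" and "Female patients in the study should continue to take these precautions for a minimum of 4 weeks after the last dose of study drug".

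Section 1.2 reports that "evidence of a genotoxic potential with BKM120 has been seen in vitro and in vivo and is likely due to an aneugenic effect". It also says that testicular toxicity in rats at the highest dose had not fully reversed after 4 weeks without treatment.

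**The concern.** The protocol asks participants to prevent conception for weeks after the last dose, but asks the site to notify a pregnancy only if it occurs during dosing. A partner pregnancy conceived 6 weeks after a man's last dose falls inside the 16-week contraception period, yet no section requires it to be notified or its outcome followed.

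At stake is safety information on pregnancies that the contraception rule is meant to avoid. The non-clinical findings in Section 1.2 make the weeks after dosing relevant. If such a pregnancy is not on file, an adverse outcome months later might not reach the trial office.

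**Working it through.** There is no stated figure to reproduce; the check compares two time windows.

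**Inputs**
- Days on drug: 14 in cohorts 1-3 and the expansion cohort, 28 in cohort 4 (footnotes to the schedules of events).
- Contraception after the last dose: 4 × 7 = 28 days for women, 16 × 7 = 112 days for men and partners (Sections 4.1 and 5.1). Both are minimum lengths.
- Required notification: days on drug only (Sections 14 and 5.1).
- Final visit: day 56, or day 70 in cohort 4. SAE reporting ends 6 weeks (42 days) after treatment (Section 13.7), which is 14 + 42 = day 56, or 28 + 42 = day 70. The two end points coincide.

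**Share of the window covered** = days on drug / (days on drug + days of contraception after the last dose)

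| Cohort | Group | Covered | Not covered |
|---|---|---|---|
| 1-3 and expansion | Women | 14/(14 + 28) = 14/42 = 33.3% | 28/42 = 66.7% |
| 1-3 and expansion | Men and partners | 14/(14 + 112) = 14/126 = 11.1% | 112/126 = 88.9% |
| 4 | Women | 28/(28 + 28) = 28/56 = 50.0% | 28/56 = 50.0% |
| 4 | Men and partners | 28/(28 + 112) = 28/140 = 20.0% | 112/140 = 80.0% |

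**Days after the final visit**
- Men, cohorts 1-3 and expansion: 126 − 56 = 70 days.
- Men, cohort 4: 140 − 70 = 70 days.
- Women: none. Their period ends on day 42 (day 56 in cohort 4), before the final visit.

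**Do other provisions close the gap?**
- Section 13.7 (SAEs up to 6 weeks after treatment): no. Section 14 counts a pregnancy as an AE or SAE only when an interaction between the drug and the contraceptive is suspected.
- Sections 13 and 13.1: in part. A congenital anomaly is an SAE by definition, and drug-related SAEs that come to light later are reportable. This needs an investigator who hears of the event and suspects the drug.
- Section 5.1, item (5): it speaks of the outcome of all pregnancies, but within a sentence about pregnancies during administration.
- Section 2.2: the follow-up channel of up to 1 year after treatment covers late radiotherapy effects only.

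None of these requires notification of a pregnancy that begins after the last dose.

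**The case against.** The strongest reply has four parts.

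First, the two rules do not contradict each other. How long to use contraception and which pregnancies to notify are separate questions, and Section 14 sets a minimum that bars no further report. That is true, but a site that follows the minimum would not have to report the pregnancies described here.

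Second, a reader might infer that most at-risk pregnancies escape reporting. The documents do not support that. The figures are shares of days, and the protocol gives no conception rate and no risk by day. With the effective half-life of about 40 hours in Section 1.2, five half-lives take 5 × 40 = 200 hours, a little over 8 days, so a woman's direct exposure is concentrated in dosing and shortly after. That does not settle the male window. For women in cohort 4 the uncovered share is exactly half, so even as a share of days the word most fails there.

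Third, a reader might infer that the 4 and 16 weeks were chosen because of the aneugenic and testicular findings. The protocol gives no reason for these lengths; the only reason it gives in criterion 21 concerns why hormonal methods are not allowed. The findings make the period relevant, but the link is an inference.

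Fourth, a reader might infer that any resulting anomaly would be missed. That is too strong, given the partial safety nets in Sections 13 and 13.1, and women still have a final visit after their 4 weeks end. What stands is that these nets depend on awareness and suspicion.

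Materiality is also fairly raised: the trial has 2 to 30 evaluable patients with incurable disease, under mandatory contraception.

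**Conclusion.** The point holds as a mismatch between two windows. Required notification covers 33.3% of the days for women and 11.1% for men and partners in cohorts 1-3 and the expansion cohort, and 50.0% and 20.0% in cohort 4. For men, 70 further days lie beyond both the last visit and the SAE window. An adverse outcome of a pregnancy conceived after dosing might therefore not be captured.

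The figures rest on three assumptions: that a pregnancy occurs at conception, that the contraception periods are taken at their minimum lengths (longer periods would lower the shares), and that cohort 4 dosing ends on day 28. One line in Section 5.4 gives day 37 for the end of treatment. With that day the cohort 4 shares would be 37/(37 + 28) = 56.9% and 37/(37 + 112) = 24.8%, and the gap would remain.

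This is a safety-reporting gap with few expected events. It does not touch the DLT definition, the MTD rule, the sample size or the imaging endpoints. It is worth correcting because each event would matter and the change is small.

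**What to change.** Reconcile Section 14 and item (5) of the Section 5.1 counselling list with the contraception periods in Section 4.1 and items (3) and (4) of that list. Notification and outcome follow-up should run from the first dose to the end of the contraception period that the protocol already requires for the patient concerned. Keep the present form, timeline and follow-up to term. At the end-of-study visit, remind male patients to tell the site of a partner pregnancy that occurs before their period ends.

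The required reporting period would then go from 14 to 42 days (women) and from 14 to 126 days (men and partners) in cohorts 1-3 and the expansion cohort, and from 28 to 56 and from 28 to 140 days in cohort 4. The uncovered share would fall to zero.

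The cost is two protocol sentences and matching patient-information text. That text needs ethics review (Section 22.1), and the change has to go through the amendment procedure (Section 22.4). No visit or test is added, and no contraception period, dose or clinical rule changes.
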